## Results

The study is registered on the ClinicalTrials.gov platform (NCT06704230). Patient recruitment commenced in September 2022 and should be completed within 3 to 4 years. At the time of this protocol’s final submission for publication, approximately 90% of the recruitment had been completed. After the including the 100th patient, the acquired data will be analyzed and the results will be published in a peer-reviewed journal within one year.

## Discussion

### Summary

To our knowledge, this is the first study to investigate the perioperative use of video goggles in patients undergoing carotid surgery under local anesthesia. Audiovisual distraction is commonly used in surgical procedures performed under local or regional anesthesia to reduce patient stress and discomfort [8,19,20]. This, in turn, may lead to reduced use of analgesics and sedatives, thereby minimizing the risk of complications and overdose [21]. In addition, such interventions can facilitate outpatient procedures, allowing patients to be discharged shortly after treatment without the need for extended postoperative monitoring because of sedation.

In vascular surgery—particularly carotid endarterectomy performed under local anesthesia—continuous monitoring of the patient is essential to detect signs of cerebral hypoperfusion when the carotid artery is clamped. Local or regional anesthesia thus provides an advantage [22]. However, for the patient, undergoing surgery in the neck region can be physically and psychologically challenging, as they must remain in a fixed position on the operating table for approximately 2 hours while being covered by a sterile drape, which is placed closely over the patient’s face and cannot be repositioned without risking a breach of sterility. Patient stress during procedures under local anesthesia can also pose a challenge for the clinical team and affect surgical outcomes. The current literature does not indicate a significant overall benefit of one anesthetic technique over the other in carotid endarterectomy; thus, the decision should be individualized [4]. This study aims to assess the feasibility of using video goggles during such procedures and to evaluate their potential in reducing patient-reported stress levels. Furthermore, there is currently no tool to predict which patients may benefit from the use of video goggles and which may not.

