## Introduction

Atherosclerosis and macroangiopathy of the internal carotid artery are common conditions in patients with elevated cardiovascular risk. Treatment of internal carotid artery stenosis is often conservative, involving risk factor modification and medication. However, when a certain degree of stenosis is reached or symptoms suggestive of stroke are present, thrombendarteriectomy and revascularization is indicated. Revascularization can be performed either through interventional angiography with stent placement or open surgical endarterectomy [1-3]. The operation is frequently carried out under regional plexus anesthesia, which allows the patient to be awake and enables continuous neuromonitoring. This approach offers the advantage of monitoring for neurological changes during carotid artery clamping, allowing the surgical team to immediately respond, for example, by placing a shunt system to ensure cerebral antegrade perfusion [4]. As a result, regional anesthesia provides a benefit during surgery. However, for patients, the procedure, which can last up to 2 hours or more in some cases, may pose a significant burden. The fixed position, inability to move, sterile drapes over the face, manipulation by the surgical team, and anxiety about potential complications are just a few of the factors that may distress patients during this operation [4]. All in all, studies of operations with local or general anesthesia show that neither technique has any advantage over the other [4]. Both types are carried out frequently. Increased sweating and reports of substantial subjective distress are not uncommon if the procedure is performed under local anesthesia. To the authors’ knowledge, there have been no previous attempts to quantify stress parameters or to reduce stress in these patients.

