### Secondary Exclusion Criteria and Adverse Events

Patients who withdraw consent after enrollment will be excluded from the study. If complications arise during surgery requiring conversion to general anesthesia, patients will also be excluded.

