### Interventions

The intervention group will receive perioperative video goggles with an audio system designed to distract patients from the surgical process and enhance their experience. The video goggles will display various nature scenes accompanied by soft music. Patients can choose from a variety of preloaded content. The device meets the requirements of the Medical Device Directive 93/42/EWG and the Austrian Medical Devices Act. The anesthesiologists, who are primarily responsible for helping the patients use the goggles, received brief online training on how to operate the device. To minimize potential confounding factors, intraoperative management is performed by a small and experienced team of anesthesiologists. Figure 1 shows the timing and parameters that will be measured during surgery.

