### Assessment of Distress

To assess patient stress, questionnaires and vital/laboratory parameters will be used. The day before surgery, after they provide informed consent, the patients will complete initial questionnaires. These include the Spielberger State-Trait Anxiety Inventory (STAI; Hogrefe Verlag), which measures both “trait anxiety” (a general predisposition to anxiety) and “state anxiety” (anxiety related to the current situation, ie, the upcoming surgery) [11]. This questionnaire is often used to measure anxiety and is seen as an indicator of distress. The score is used in many types of analysis, although the trait sections of the STAI are believed to measure negative affectivity rather than trait anxiety per se [12,13]. Additionally, patients will complete the Kurzfragebogen zur aktuellen Beanspruchung (KAB; German for “short questionnaire for acute stress”), which will be repeated perioperatively multiple times to assess changes in response patterns [14]. The focus will be on individual stress trajectories and differences between the control and intervention groups.

For a more objective measurement of stress, the cortisol level in the serum is measured by taking blood samples at multiple times (at baseline, arrival in the operation room, skin incision, clamping the carotid artery, skin suture, and 1 hour after skin suture). Baseline measurements are all taken under consistent conditions: the same time of day before the patient rises from bed. Resting heart rate, KAB score, and the Richmond Agitation-Sedation Scale (RASS) score will be evaluated simultaneously with blood sampling. Cortisol levels are a common tool to measure stress in acute situations [15-17]. The RASS, commonly used in anesthesiology and intensive care, will be used to estimate patients’ agitation and provide insight into their stress levels [18]. Heart rate and RASS scores serve as objective measures of patient stress, while the KAB reflects patients’ subjective burden across 6 categories. This score is frequently used in psychology to capture current stress levels and is well suited for perioperative use due to its ease of administration. The differences in serum cortisol levels between the groups are considered the primary end point. All other measurements are secondary end points.

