### Outcomes

#### Primary Feasibility Outcomes

Patients who meet the inclusion criteria and agree to participate are enrolled in the study. Patients who meet the criteria but decline participation are counted anonymously, with differentiation between those who refuse and those who are excluded for other reasons (eg, language barriers, profound hearing impairment, dementia, or logistical challenges). After the operation is completed and the patient leaves the wake-up room, all data are checked for completeness, and an attempt is made to fill in any missing data. If there any adverse events or remaining missing data, or if the patient withdraws consent to participate in the study, the collected data are excluded from analysis. Because of the very short time from patient inclusion to complete data collection for each patient and because there is no follow-up after the initial inpatient stay, we assume that this method will yield mostly complete records.

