### Strengths, Limitations, and Dissemination

To evaluate patient stress, we use a multimodal approach that includes objective and subjective parameters. Serum cortisol levels serve as the primary objective marker, complemented by heart rate monitoring and the RASS. Additionally, the KAB questionnaire was used to assess patient-perceived stress. All parameters were recorded at multiple time points before, during, and after the operation, enabling a comparative analysis comparing the intervention and control groups.

Drug administration was meticulously documented, as medications could potentially confound the measured parameters. Although the sample size is limited, which may preclude statistically significant findings, and this is a single-center study, which means that just one device in one specific procedure is evaluated, the study primarily aims to assess the feasibility and acceptance of video goggles by patients, anesthesiologists, and surgeons, as well as to identify robust parameters for future research. By publishing our findings in a peer-reviewed journal, we hope to provide a basis for further research in this field and to promote enhanced approaches to perioperative stress reduction in patients undergoing carotid surgery under local anesthesia. In future work, a potential third group using music as a distraction tool could be explored.

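### Conversions to general anesthesia and patients with adverse events are dropped from the analysis, so the feasibility results would rest on complication-free patients

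*Protocol article*

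**What the plan says.** **Why the patient is awake.** The Introduction says that regional anesthesia permits "monitoring for neurological changes during carotid artery clamping, allowing the surgical team to immediately respond, for example, by placing a shunt system". The Discussion (Summary) goes further: "continuous monitoring of the patient is essential to detect signs of cerebral hypoperfusion when the carotid artery is clamped".

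**What is tested.** Interventions describes "perioperative video goggles with an audio system designed to distract patients from the surgical process".

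**What the study is for.** Strengths, Limitations, and Dissemination states that "the study primarily aims to assess the feasibility and acceptance of video goggles by patients, anesthesiologists, and surgeons"; identifying parameters for later research is a further aim. The formal end point is different. Assessment of Distress says: "The differences in serum cortisol levels between the groups are considered the primary end point. All other measurements are secondary end points".

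**Who leaves the analysis.** Secondary Exclusion Criteria and Adverse Events: "If complications arise during surgery requiring conversion to general anesthesia, patients will also be excluded". Primary Feasibility Outcomes has a second rule, opening "If there any adverse events or remaining missing data", under which the patient's collected data are left out of the analysis. It sets no limit by seriousness or by relation to the device.

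**What is still reported.** Data Collection and Management promises that the arm and the reason for each exclusion will be disclosed.

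**The concern.** Whether a distraction device is feasible in awake carotid surgery depends partly on the operations that did not go to plan: those converted to general anesthesia, those with an adverse event, and those in which the team had to react to a neurological change. The first two groups are removed from the analysis by rule, and the third is not among the outcomes the article lists.

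If the plan is followed as written, satisfaction, willingness to reuse the goggles, staff ratings and any feasibility statement will describe complication-free patients only. Exclusion depends on events after randomisation, so the two arms may also be depleted unequally. According to Sample Size Estimation, the results are meant to be the basis for a confirmatory trial, so a feasibility conclusion that is too favourable would be carried into its design.

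**Working it through.** **Inputs.** 100 patients allocated 1:1, so 50 per arm (Randomization). Sample Size Estimation says that no formal calculation was made, so there is no planned figure to reproduce. The document gives no rate for conversion, shunt, neurological event or adverse event. The rates of 1% to 10% below are assumptions.

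**Step 1: outcomes set against the aim.**
- Primary Feasibility Outcomes covers enrolment, refusals and reasons for non-participation, and completeness of records.
- Assessment of Distress covers cortisol, heart rate, KAB, RASS and STAI.
- Assessment of Usefulness and Practicality covers patient ratings of satisfaction and anxiety, staff ratings of manageability, relaxation and calmness, willingness to reuse the goggles, and motion sickness.
- None of these records neurological change at clamping, shunt placement, or removal or pausing of the goggles. The closest are RASS and KAB at clamping and the manageability rating. The article presents RASS and KAB as stress measures and groups manageability with calmness.

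**Step 2: what the exclusion rules do.** By construction the analysed set holds 0 conversions and 0 adverse events per arm at any true rate. Invented example: 3 conversions with goggles and 1 without. The analysed arms become 50 − 3 = 47 and 50 − 1 = 49, each with 0 conversions. The 3 and the 1 could appear only in the list of exclusion reasons.

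**Step 3: how likely the rules are to bite.** The chance of at least one affected patient among 50 is 1 − (1 − p)^50:

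| Assumed p | Expected in 50 | Chance of at least one |
|---|---|---|
| 1% | 0.5 | 39% |
| 2% | 1.0 | 64% |
| 5% | 2.5 | 92% |
| 10% | 5.0 | 99% |

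**Step 4: what could be learned if the patients were kept.** The exact two-sided 95% upper limit for 0/50 is 1 − 0.025^(1/50) = 0.071, or 7.1%. The one-sided 95% limit is 1 − 0.05^(1/50) = 0.058, or 5.8%. The exact (Clopper-Pearson) two-sided intervals are 0.05% to 10.6% for 1/50 and 1.3% to 16.5% for 3/50.

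**Step 5: whether a test is realistic.** At 50 per arm and two-sided 5%, power is about 17% for 2% versus 6%, 15% for 5% versus 10%, and 38% for 5% versus 15%. By-arm counts with intervals are useful; a significance test would not be.

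**The case against.** The strongest reply is that the information is not lost. Data Collection and Management promises disclosure of the arm and reason for each exclusion, so a reader of the results should see how many patients in each arm left because of conversion or an adverse event. This stands. A reader might infer that 3 versus 1 conversions would be published as 0 and 0, or that the trial would yield no evidence on these events. The document does not support either: the zeros apply to the analysed set only. But a list of exclusion reasons is not a feasibility outcome, does not cover neurological change or shunting in patients who stayed in, and does not change the set on which acceptance is judged.

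A second reply is that the article condenses a fuller, ethics-approved protocol, where safety items and case report form fields would normally sit. This also has force. The lack of a dedicated monitoring outcome here does not prove that none exists, so the point rests mainly on the exclusion rules, which the article does state.

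Third, RASS and KAB are taken at clamping, and a patient who answers a questionnaire at that moment is responsive. Together with the manageability rating, these are indirect proxies. They do not record neurological status.

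Finally, one might infer that the goggles impair monitoring, or that this is the trial's declared safety question. The document says neither. It names no safety objective, states that the study leaves operative and anesthetic management unaffected, and shows the period of goggle use only in a figure that is not available here.

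**Conclusion.** The concern holds in a limited form. Two stated rules remove converted patients and patients with adverse events from the analysis of a study whose declared main aim is feasibility, in an operation for which it calls awake monitoring at clamping essential. The feasibility and acceptance results would then describe complication-free patients.

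The size cannot be fixed from the document. Under assumed rates of 1% to 10%, the chance that at least one of 50 goggles patients is affected runs from 39% to 99%. Even with every patient retained, 0/50 would leave rates up to 7.1% open. The figures assume 50 patients per arm and independent events.

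The finding is not that the goggles are unsafe, nor that the report will be silent on conversions. It is that the stated analysis set does not match the stated aim. This should be corrected before analysis. The article puts recruitment at about 90% at submission, with analysis to follow the 100th patient.

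**What to change.** - **Reconcile the rules with the aim.** Amend Secondary Exclusion Criteria and Adverse Events and Primary Feasibility Outcomes so that conversion or an adverse event does not remove a patient from the feasibility and safety analysis, and so that an incomplete record does not do so either. How these patients enter the cortisol comparison is a separate decision.
- **Add one descriptive table by arm**, for all randomised patients whose consent allows it: conversion to general anesthesia; adverse events, including perioperative neurological events; neurological change at clamping; shunt placement; and goggles removed or paused, where documented. Give counts with exact 95% confidence intervals and no test. If 0/50 is seen, print the 7.1% upper limit beside it.
- **Use existing operative and anesthesia records** where they can still be linked. Ethical Considerations describes the data as anonymized, so linkage may fail for some patients; state how many in each arm.
- **Limit the feasibility wording** to what these counts support.

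The cost is extraction of a few items for about 100 patients and one table, with no new visit or procedure. The intervals will be wide. Shunt counts need care in reading: a shunt may mean that a deficit was detected, and fewer shunts may reflect chance or a missed deficit, so they do not by themselves show whether monitoring worked.

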### Strengths, Limitations, and Dissemination

To evaluate patient stress, we use a multimodal approach that includes objective and subjective parameters. Serum cortisol levels serve as the primary objective marker, complemented by heart rate monitoring and the RASS. Additionally, the KAB questionnaire was used to assess patient-perceived stress. All parameters were recorded at multiple time points before, during, and after the operation, enabling a comparative analysis comparing the intervention and control groups.

Drug administration was meticulously documented, as medications could potentially confound the measured parameters. Although the sample size is limited, which may preclude statistically significant findings, and this is a single-center study, which means that just one device in one specific procedure is evaluated, the study primarily aims to assess the feasibility and acceptance of video goggles by patients, anesthesiologists, and surgeons, as well as to identify robust parameters for future research. By publishing our findings in a peer-reviewed journal, we hope to provide a basis for further research in this field and to promote enhanced approaches to perioperative stress reduction in patients undergoing carotid surgery under local anesthesia. In future work, a potential third group using music as a distraction tool could be explored.

### Conclusions

This pilot study explores the implementation of video goggles during carotid surgery under conscious sedation and aims to identify suitable outcome parameters for evaluating this interventin’s potential benefits in reducing perioperative stress.

## Abbreviations

KAB: Kurzfragebogen zur aktuellen Beanspruchung; German for “short questionnaire for acute stress”
NRS: numeric rating scale
RASS: Richmond Agitation-Sedation Scale
STAI: Spielberger State-Trait Anxiety Inventory
